### Concealment mechanism {16b}

Clusters (communities) will be randomly allocated to intervention and control group by the study statistician using a digital sealed envelope. This will be done after the collection of baseline data and just before the commencement of the intervention phase.

### Implementation {16c}

This is a cluster-randomized trial. Clusters or communities will be randomized and not individual participants. Allocation will be done by the statistician while participants will be enrolled by CORPS and health workers at the primary health centres.

## Assignment of interventions: Blinding

### Who will be blinded {17a}

Given the nature of the intervention, it is not possible to blind the CORPs who will be involved in the delivery of the intervention. However, the interviewers who will collect data for final assessment and the statistician may be blinded.

### Procedure for unblinding if needed {17b}

The design is open label with only outcome assessors and the statistician being blinded so unblinding will not be applicable.

## Data collection and management

### Plans for assessment and collection of outcomes {18a}

Standard operating procedures will be developed for each of the data collection activities to guide the research assistants and standardized the collection methods. Survey interviews will be conducted by 10 trained interviewers who will be graduates of tertiary institutions with experience in conducting community-based surveys and qualitative studies. Interviews will be conducted in secluded areas in the participants’ houses and at a convenient time of the day. Participants will be given a sachet of detergent to compensate for the time of the interview.

#### Quantitative data collection

Surveys will be conducted using the Research Electronic Data Capture (REDCap) software on Android mobile devices. The data collection tools will be developed using information from literature, consideration of variables in the study-specific objectives and the conceptual framework, researchers’ knowledge of the topic and adaptation of questions from past related studies. A semi-structured question will be drafted and face validated by experts to ensure the questions are adequate to provide answers to the study objectives. The draft questionnaire will be pre-tested in a community not selected in each of the six LGAs to ensure that questions are clear, comprehensible by participants, concise and consistent in a local government different from the ones selected into the study. The Cronbach alpha acceptable value will be set at 0.7 and above. The questionnaire will be translated into the local language and back translated into English to ascertain the correctness of the translation.

The survey questionnaire will be divided into the following sections: (a) demographic characteristics, (b) health status of the participants including, presence of chronic disease(s), knowledge of their blood pressure status, drug history, (c) health-seeking behaviour, (d) disease screening practices, (e) lifestyle including dietary habit, (f) knowledge of hypertension, risk factors and its control including sources of information, (g) cost of treatment of hypertension among those with hypertension, (h) willingness to accept CORPs to screen for hypertension and carry out follow-up care for hypertension in the community

#### Clinical and anthropometry measurements

##### Blood pressure

Blood pressure will be measured using a fully automated digital device, the OMRON digital sphygmomanometer (OMRON HEM-712C). Interviewers will be trained to use the device according to the manufacturer’s recommended protocol, and BP will be measured using recommended methods and categories from standard guidelines such as the World Health Organization-International Society of Hypertension Guidelines for the Management of Hypertension. The first blood pressure reading will be measured on the left arm with the participant in a seated position after resting for at least 5 min. The second and third readings will be taken about 2-min interval. In this study, hypertension was defined as average of two measurements of systolic and/or diastolic BP (2nd and 3rd readings) that is ≥140/90 mmHg in any adult according to the Joint National Committee JNC7 classification or self-reported previous diagnosis of hypertension and treatment of hypertension with antihypertensive medication taken in the past 2 weeks [34]. Participants with elevated blood pressure will be referred to a health facility for further assessment and confirmation of the BP status.

##### Electrocardiogram examination

The electrocardiogram (ECG) is listed among the routine investigation for hypertensive patients according to international guidelines. It has been used for the evaluation of subclinical cardiac damage in uncomplicated hypertensive patients [35]. The outcome could help with stratification of cardiovascular risk in hypertension. In this study, individuals confirmed to have high blood pressure shall have electrocardiogram (ECG) examination at baseline and endline. Those with abnormality shall be referred to a cardiologist in the nearest hospital.

##### Behavioural risk factors

The WHO STEPwise data collection tool for surveillance of non-communicable diseases will be adapted to gather information on behavioural CVD risk factors including smoking, alcohol drinking and dietary habits [36]. Questions will probe on current and past smoking as well as current and past alcohol drinking. Dietary assessment will include intakes of fruits, vegetables, salt, use of vegetable cooking oil and consumption of whole grains.

##### Anthropometric measurements

Anthropometric measurements will include weight, height and waist circumference taken using standard procedures. Briefly, all anthropometric measurements will be taken with the participant wearing light clothing and without shoes within the participant’s household compound. Body weight will be taken to the nearest 0.1 kg using a validated SECA digital scale placed on flat ground. Height will be taken in a standing position with heels perpendicular to the portable stadiometer, measured to the nearest 0.1 cm. BMI will be calculated as body weight divided by height squared (kg/m^2^). Overweight will be defined as BMI ≥ 25 kg/m^2^ but < 30 kg/m^2^ and obesity is defined as BMI ≥ 30 kg/m^2^ [36]. Waist circumference will be measured and recorded to the nearest 0.1 cm using a non-stretchable measuring tape at the mid-point between the lower margin of the last rib in the mid-axillary line and the iliac crest according the WHO guidelines [37]. Abdominal obesity will be defined as waist circumference ≥ 102 cm. Waist-to-hip ratio will be calculated and a value of less than 0.85 is considered as normal for women and less than 1.0 for men is normal.

##### Wealth index

The household wealth index of the participants will be generated as described in the demographic health survey using data on ownership of household items such as refrigerator, bicycle, radio, television, sofa, telephone, car and house ownership, construction materials (floor, walls and roofing materials); source of water supply for home use and drinking; source of fuel for cooking and lighting; and having working electricity and sanitation facility [38].

## Qualitative data collection

The guide will be developed for the focus group discussion (FGD) and key informant interview (KII). A pre-tested guide will be used to facilitate the FGD sessions and KII interviews. The sessions will be audiotape recorded after obtaining consent from the participants. The FGD will be conducted by a team of 2–3 research assistants—facilitator, note-taker / recorder. Snacks will be provided during the sessions.

Key informant interviews will be conducted among key people in the community, head of facilities, the physician, or health workers involved in the management of hypertensive patients. The focus group will comprise 6–12 homogenous community members. Two research assistants will facilitate the session. Participants will be provided incentive to compensate for the time at the FGD.

## Development of intervention materials

Results from the preliminary analysis of the baseline study data will help to identify gaps in the awareness, knowledge, perception, attitude and preventive practices regarding hypertension. This information will be used for the development of the intervention materials by the team members. These materials include (i) training manual for CORPs and health workers, (ii) information education communication/behaviour change communication (IEC/BCC) materials including healthy lifestyle hand bills, hypertension treatment guide, (iii) home-based follow-up care guide, (iv) standard operating procedures, (vi) short messaging system (SMS) messages.

## Training manual and guides

Training manuals will be designed adopting the relevant sections in the WHO training manual for the prevention of NCDS and health lifestyle [39] and manuals shared by researchers who have conducted similar studies. The training topics will include definition of hypertension, risk factors, detection and management, blood pressure screening procedures and interpretation of readings, anthropometric measurements, ethical issues, community mobilization and effective communication for behaviour change, health education on hypertension and healthy lifestyle and follow-up care for hypertension among others. Graphics and pictorials will be used as appropriate. The manual will be face validated by two researchers involved in hypertension studies. In addition, guides will be developed using algorithms and adapting the National Hypertension Control guidelines.

## Health education materials

The health education materials will be developed by team members using illustrations from literature, adapted from IEC materials shared by other researchers and drawn by an artist. The draft will be presented to CORPs and health workers for their input after which it will be face validated by selected community members before final production. The materials will be in form flyers/brochures with messages on hypertension as silent killer, the risk factors and how to prevent them such as reducing salt intake, reducing or maintaining normal/ideal body weight, smoking cessation, reducing alcohol intake, increasing consumption of fruits and green leafy vegetables, using vegetable cooking oil and engaging in exercise. Training modes will include didactic lecture, case study, role plays and practical sessions in the field.

### SMS message

The content of reminders will be prepared based on literature search and consultations with communication expert. A SMS reminder content of about a minute duration will be designed. The message will be prepared in English and translated to local languages (Hausa, Igbo and Yoruba) version; thereafter, back translated to English to verify accuracy of the translation by an expert in both English and the local languages. It will be validated and pre-tested among 10 selected members of communities not included in this study.

### Plans to promote participant retention and complete follow-up {18b}

Participants will be provided adequate information on the project and their role as well as what is expected of them emphasizing completeness of follow-up. It will be ascertained at time of recruitment that the participant will be resident in the community for at least a year. The participants will be linked to the CORPs in their community who will provide follow-up care and visit them to check on adherence to clinic follow-up visit. The participant is recruited from the catchment area of the clinic; hence, it is assumed that this will encourage clinic as distance to clinic will not be a barrier to follow-up visit. The proportion of participants who visit the clinic and those who had home follow-up visit by CORPs as scheduled shall be measured at the end of the 6-month follow-up visit.

### Data management {19}

The research assistants (data collectors) will upload the data collected on their android phone daily into the REDCap database server from where the data manager will retrieve and review the data daily for quality assurance and control. The data manager will provide feedback on entered data early the following morning they were collected so that research assistants can correct wrong entries and fill gaps or missing data as necessary.

For the qualitative data, the audio recording will be carried out using a good quality tape recorder and research assistants will ensure it is functioning, label the sides and pre-record to test before use for the sessions. The tapes will be kept in locked boxes to prevent destruction and for confidentiality. Analysis will be carried by two investigators independently. Where they differ, the transcribed notes will be revisited and analysed again till there is a consensus.

### Confidentiality {27}

#### Handling and storage of data

The confidentiality of all participants information will be protected in accordance with national and international data protection laws. The study team will assure that participants’ anonymity will be maintained and that their identities are protected from unauthorized parties.

Participants will be assigned unique code as identification numbers for data collection. All information will be collected using the unique study participants’ code numbers except for consent forms, which will bear the name and signature of the participant. Only the statistician and data manager have access to the files in the REDCap. Documents (i.e. participant signed ICF, medical records, case record forms) will be maintained in strict confidence in passworded files on the computers and locked cabinets in the office. Any reports or publications or scientific presentations will not contain any participants’ identifying information. The data will be in storage for at least 5 years and any request to use them for secondary data analysis shall be made to the principal investigator after agreeing to conditions for data sharing and all data will be de-identified.

### Plans for collection, laboratory evaluation and storage of biological specimens for genetic or molecular analysis in this trial/future use {33}

Ready-to-eat food samples will be collected randomly at unannounced visit to a participant’s home twice (including one weekend day) during the study and kept frozen in a sterile bottle. Biochemical analysis of food sodium content will be carried in certified laboratories such as the International Institute of Tropical Agriculture, (IITA) Ibadan, Nigeria.

Blood samples for estimation of urea, creatinine and lipid profile will be collected according to standard laboratory guideline under sterile conditions at recruitment and at the end of the 6-month intervention period in the health facility. Urine samples will also be collected and analysed using Uristix® at the same time. Blood sample analysis will be at the Chemical pathology laboratory of a tertiary institution in the study states.

## Statistical methods

### Statistical methods for primary and secondary outcomes {20a}

Data analysis will be carried out using Stata MP version 14 based on the CONSORT 2010 guideline [40]. Intention-to-treat analysis will be applied. Continuous variable will be presented as mean and standard deviations (SDs) or medians with their 25th and 75th percentiles when the distribution of the data does not follow a Gaussian distribution. Categorical variables shall be presented as frequencies and percentages.

Baseline characteristics of participants in the intervention and control arms will be compared to assess balance and identify any variable that need to be adjusted in the final analysis. The primary outcome is achievement of blood pressure control at 6 months post-intervention. The effect of intervention within each of the study groups will be carried out comparing baseline and 6 months post-intervention using McNemar test. Depending on the distribution of baseline characteristics, random effect logit model will be fitted to estimate treatment effect size comparing the two groups. Similar analysis will be done for categorical secondary outcomes such as treatment adherence.

Cost-effectiveness analysis will also be carried out using the ingredient approach [41].

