## Methods: participants, interventions and outcomes

### Study setting {9}

The study will be conducted in three states selected from the six geopolitical zones in Nigeria comprising of Abia (South East), Kano (North West) and Oyo (South West) states. A state in Nigeria comprises a number of LGAs and each LGA is made up of 10 to 12 wards.

Two Local Government Areas (LGAs) (one urban and one rural) each were selected from each state based on participation in past hypertension survey and good cooperation received from the community members in past studies. Thus, in Abia State—Umuahia North (urban) and Isuikwuato (rural) with population of 292,300 and 151,700; in Kano state—Tarauni (Urban) and Bichi (Rural) with population of 387,100 and 308,600; and in Oyo state—Ibadan North (Urban) and Ona-Ara (Rural) with population of 473,900 and 373,100 respectively will be studied [31]. Figure 2 is the map of Nigeria showing selected states visited.

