## Assignment of interventions: allocation

### Sequence generation {16a}

The unit of randomization will be the community. A total of 10 communities (five from each LGA) will be randomly selected from the list of communities from a ward obtained from the Local Government secretariat. The selected communities from each LGA will be grouped into two non-contiguous groups based on geographical distance between communities. One group will be randomly assigned to intervention and another to control. This will ensure that intervention communities are closed together but at far distance from control communities to minimize contamination. The final randomization of intervention and control communities will be done by a statistician who is not involved in the implementation of field activities. Assignment of communities to either the intervention or control arm will be done after the baseline survey. Given the nature of the intervention, it is not possible to blind the CORPs who will be involved in the delivery of the intervention.

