### Methods in analysis to handle protocol non-adherence and any statistical methods to handle missing data {20c}

The use of CORPS who are based in the study communities and monthly home visit will help to minimize the occurrence of missing data and losses to follow-up. During analysis, sensitivity analyses will be carried out to assess the patterns of missing data and loss-to-follow-up so that appropriate decisions can be taken on whether multiple imputation methods need to be employed. The level of significance will be set at 5%.

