The population characteristics of the urban and rural areas could differ especially with age and sex bearing in mind population migration factors and dynamics. This may distort the true effect of the intervention on outcome as CVD risk factors varies in these groups of people. This will be adjusted at analysis using multilevel analysis with random effect model. Bias in the intervention study will be minimized by randomization. The possible contamination between control and intervention arm will be reduced by grouping/clustering the communities before randomization and ensuring buffer zones exist between them to limit diffusion.

Cluster-randomized design is appropriate for this study which by nature is evaluating the effectiveness of an interventions in a “real-world setting” [48], and meant to provide health education at both community and individual levels. In addition is the fact that it is also an effective way to avoid contamination. The limitations associated with its use such as prevention of interference shall be giving much attention at analysis.

In conclusion, this study stands to provide evidence-based information for scaling up task sharing as well as community-clinical linkage in the control of hypertension in Nigeria. It is expected that this intervention will bring about early detection of hypertension, reduction in mean blood pressure and an increase in the proportion of patients with controlled blood pressure. In addition, we expect an improvement in the mean quality of life score; healthy lifestyle and competent CORPs as well as the reduced mean cost of treatment of hypertension in the intervention arm of the study. All of these will inform policy review to guide the control of hypertension and reduction in cardiovascular diseases risk in Nigeria.

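### A baseline comparison of the arms, with no stated criterion, decides the covariates of the primary between-arm model, so entry blood pressure may be left out

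*Protocol article*

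**What the plan says.** In the protocol article, section {20a} names the endpoint: "The primary outcome is achievement of blood pressure control at 6 months post-intervention". Baseline characteristics of the two arms are to be "compared to assess balance and identify any variable that need to be adjusted in the final analysis". The between-arm analysis then follows: "Depending on the distribution of baseline characteristics, random effect logit model will be fitted to estimate treatment effect size comparing the two groups". No covariate is named for that model, and no criterion for balance is given.

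The only significance threshold for the analysis is a general one, in the section on non-adherence and missing data {20c}: "The level of significance will be set at 5" per cent. It is not tied to the baseline comparison.

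On allocation, Study setting {9} says "Two Local Government Areas (LGAs) (one urban and one rural) each were selected from each state", and there are three states. Sequence generation {16a} says "The selected communities from each LGA will be grouped into two non-contiguous groups based on geographical distance between communities", and then "One group will be randomly assigned to intervention and another to control".

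Two other places bear on adjustment. The Discussion, on urban and rural populations that differ especially in age and sex, says "This will be adjusted at analysis using multilevel analysis with random effect model". The section on additional analyses {20b} plans a difference-in-difference analysis and a linear mixed model for mean systolic pressure.

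**The concern.** Under this rule a covariate enters the primary model because the arms happen to differ on it, not because it predicts the outcome. Systolic pressure at entry is an obvious predictor of control at 6 months, yet it is adjusted for only if the comparison picks it out. LGA is the stratum of allocation. It is balanced by design at 50 patients per arm in each LGA (Sample size {14}), so a balance check would not be expected to select it.

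Three things are at stake:

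- A blood pressure imbalance that goes unselected shifts the estimated effect in that allocation.
- The precision that entry pressure offers is lost when it is left out.
- The form of the primary model, and on a literal reading whether it is fitted at all, stays undecided until someone has looked at the baseline data.

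**Working it through.** The plan gives no figure on this point to reproduce. It states no SD, ICC or correlation for blood pressure, so those below are assumptions, shown over a range.

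**Allocated units.** 3 states × 2 LGAs = 6 LGAs. Each has 2 groups, so there are 12 groups in 6 pairs. With 50 patients per group there are 300 per arm.

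**If the comparison respects clustering and uses 5%.** In SD units, the standard error of the arm difference is SE = √(2 × [ICC + (1 − ICC)/50] / 6). The miss rate comes from the noncentral t distribution with noncentrality (difference / SE). It uses 10 df for an unpaired comparison of 12 groups (12 − 2) or 5 df when paired by LGA. The last column is the chance that random allocation alone gives an imbalance of at least 0.25 SD, 2 × [1 − Φ(0.25/SE)].

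| ICC | SE | Misses 0.25 SD (10 df to 5 df) | Misses 0.5 SD | Chance of ≥0.25 SD |
|---|---|---|---|---|
| 0.01 | 0.100 | 38–47% | 1–2% | 1% |
| 0.02 | 0.115 | 50–58% | 3–7% | 3% |
| 0.05 | 0.152 | 68–73% | 16–25% | 10% |
| 0.10 | 0.198 | 79–82% | 38–47% | 21% |

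**If the comparison is patient-level and ignores clustering.** With SD 18 mmHg it flags differences above 1.96 × 18 × √(2/300) = 2.9 mmHg, so an observed 4.5 mmHg would be caught. But the variance is understated by 1 + 49 × ICC, which is 1.49 at ICC 0.01 and 3.45 at 0.05. A nominal 5% test then flags a variable by chance in 2 × [1 − Φ(1.96/√1.49)] = 11% and 2 × [1 − Φ(1.96/√3.45)] = 29% of allocations. The error is now over-selection.

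**What an unadjusted imbalance does.** Take SD 18, a slope of 0.5 from entry to 6 months and a mean 6-month pressure of 143 mmHg. Then 0.25 SD = 4.5 mmHg, and 4.5 × 0.5 = 2.25 mmHg at 6 months. The normal density at 140 mmHg is 0.0219 per mmHg, so the control rate shifts by 2.25 × 0.0219 = 4.9 percentage points.

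**Chance imbalance and type I error.** This was simulated with 200,000 allocations of 6 pairs, SD 20, no treatment effect and a baseline to follow-up correlation of 0.5 to 0.8. An imbalance above 3 mmHg arose in 13% of allocations at ICC 0.01 and 32% at ICC 0.05. Of these, 71% and 85% were not significant in a paired 5% test. Within those unflagged cases, the unadjusted test of systolic pressure had type I error of 9–11% and 7–8%. Over all allocations it stayed at 5%.

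**Precision.** This was simulated with baseline ICC 0.03, residual ICC 0.02 and no variation between LGAs. Fixed adjustment reduced the SD of the estimated risk difference from 0.052–0.053 to 0.047. Using the midpoint, (0.047/0.0525)² = 0.80, so the variance is about 20% lower.

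**The case against.** The strongest reply is that the text says less than it can be made to say. Four stronger readings are tempting, and the document supports none of them.

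- **That a non-significant difference is taken as proof of balance.** Section {20a} speaks only of comparing. It names no test, and the 5% level stands elsewhere as a general level. The cluster-aware 5% test above is one possible reading.
- **That relevant imbalances will be missed.** They can be. It depends on the unstated criterion, since a patient-level comparison would catch about 2.9 mmHg. A chance imbalance of 0.25 SD or more is itself uncommon at low ICC: 1% of allocations at 0.01, rising to 21% at 0.10.
- **That the rule inflates type I error.** Chance imbalance does not do so overall.
- **That LGA is ignored, at a large cost in power.** The level of the random effect is not stated, so the omission of LGA is not established. Any loss from leaving LGA out is also a separate matter from the balance rule.

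It can also be said that adjustment is promised elsewhere. The Discussion does commit to adjusting for urban and rural differences, and {20b} uses baseline systolic pressure for mean change. Neither fixes entry pressure in the model for blood pressure control, and a random intercept does not remove a difference in entry pressure between arms.

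Finally, a covariate list is often left to the analysis plan. That would answer a complaint of silence. Here the article states a rule, and the rule is the problem.

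**Conclusion.** The point holds in a limited form. The article sets a data-driven choice of covariates for the primary between-arm model, gives no criterion for it, and words even the fitting of that model as conditional on the baseline distribution. That much rests on the text alone.

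The size rests on assumptions. With 12 allocated groups and ICC 0.01 to 0.10, a cluster-aware 5% comparison misses a 0.25-SD difference 38% to 82% of the time. With SD 18 mmHg and slope 0.5, such a difference is worth about 5 percentage points of control rate. A comparison that ignores clustering errs the other way. Either way, which model is fitted depends on an unstated judgement made after seeing the data. The consequences are conditional bias, lost precision and avoidable discretion. This should be changed, but it does not invalidate the trial.

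**What to change.** In {20a}, replace the balance-driven selection. State that the random-effect logit model for blood pressure control will always be fitted, with participant-level systolic pressure at recruitment as a fixed covariate and the LGA stratum of allocation accounted for, whatever the baseline table shows. Apply the same rule to the linear mixed model in {20b}. Name any further covariates, such as age and sex, in advance and keep them few. Use the baseline table for description only.

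This takes a sentence or two. It needs no new patients or visits, because the plan's own within-arm comparisons already require blood pressure at baseline, and LGA is known. Trial status says that recruitment for the intervention had not started, so the change could be made before trial baseline data were seen.

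The cost lies in degrees of freedom. Six LGA fixed effects use 5 of about 10 at group level. In a group-level simulation with a true difference of about 17 points, power with fixed entry pressure was about 92% without LGA effects and 85–86% with them. With LGA kept in both analyses, adjusting only after a flagged imbalance gave about 76%. Accounting for LGA can therefore cost some power if LGAs differ little, while fixing entry pressure in the model gains power.
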